### Sample size

Sixty patients (30 in the film + exercise hospital, 30 in the exercise-only hospital) will be recruited. Thirty patients per study site is the minimum recommended for early phase studies to provide reasonable estimates of efficacy on outcomes (estimating means and variances) [68–70]. A total sample size of 60 will facilitate building a multivariable model with up to 3 covariates plus 3 main factors (hospital, time, and hospital X time). Moreover, with alpha = 0.05 and power of 80%, we would need about 30 patients per arm to detect a 0.65 SD difference between hospitals in the 2MWT, our primary quantitative outcome. A 0.65 SD difference represents a moderate effect size and is equivalent to about 22 m, which is larger than the minimum clinically important difference for the 2MWT [71]. Based on the pilot study with older HD patients [19] conducted by several co-investigators, there was 0 attrition over the duration of the exercise program. Although we recognize that the observed attrition rate may be higher than this in the present study, estimating attrition is a specific aspect of feasibility that we will be evaluating in this phase of the research. Sample size calculations for early phase studies commonly do not include adjustments for attrition [68–70].

Patients (*n* = 20; 10 per site), family caregivers (*n* = 20; 10 per site), nephrologists (*n* = 10; 5 at each site) and nurses (*n* = 20; 10 at each site) will be selected to participate in qualitative semi-structured interviews (Section 4.5.1). Sample sizes are consistent with what is deemed sufficient for qualitative sampling in a homogeneous group within a single setting, and provides a sufficient number of participants to facilitate saturation [72].

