To explore the impact of *Fit for Dialysis* on patient fitness and activity outcomes, while keeping in mind the phase of research, our focus is to estimate change in each of the 6 measures using a hospital X time linear repeated measures model for each outcome. The 2MWT is our primary outcome. Examining hospital-level effects will allow us to determine if the two hospitals were similar at baseline. Examining time effects within each hospital will provide information on the effects of the intervention in that hospital (film + exercise or exercise-only). Additionally, examining the hospital X time interaction will allow us to determine the additional effect of the film in addition to the exercise intervention. Since this is an early-phase intervention trial and it is unclear which of our quantitative outcomes will be most responsive in this population, we will also examine the responsiveness of each of the 6 outcome measures using standardized response mean to gauge whether the film + exercise is associated with a small, moderate, or large effect size [78] for each outcome. Covariates will be similar to Primary Objective 2. To examine the impact of adherence on the 2MWT, we will include a dichotomous variable reflecting global (intradialytic and home/community-based exercise considered together) adherence (yes/no). We will also explore including the two separate adherence components (intradialytic and home/community) in the repeated measures model, recognizing the risks of collinearity and model over-fitting (with 8 variables and 60 patients, including an interaction term between the two adherence variables).

As an exploratory analysis to get an initial sense of the temporal effects of both the film and the exercise program, we will calculate change scores for each of the 6 measures from baseline to 8 weeks, from 8 to 16 weeks, and from 16 weeks to 12 weeks after the end of the intervention (i.e. 28 weeks after baseline). An additional exploratory analysis will examine the six outcome measures (DASI, GLTEQ, TUG, 2MWT, Grip Strength, and pedometer) at 12 weeks after the end of the intervention. This analysis will consist of a linear repeated measures model similar to above, with two time points (8 and 16 weeks) and 12 weeks follow-up, and will examine whether any observed gains during the intervention period persist, continue to improve further, or become attenuated over time in both the film + exercise and exercise-only hospitals.

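### The 80% power quoted for 0.65 SD with 30 patients per arm matches a simple two-group comparison only with an undeclared one-sided alpha; at two-sided 0.05 the power is about 70%

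*Protocol article*

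**What the plan says.** The Sample size section gives three reasons for 60 patients: 30 per site is presented as a recommended minimum for early-phase work, 60 in total supports a model with a limited number of terms, and there is a power statement. The power statement reads "with alpha = 0.05 and power of 80%, we would need about 30 patients per arm to detect a 0.65 SD difference". The comparison meant is of the two sites on the 2MWT, which the section names as the primary quantitative outcome. It adds that this difference "is equivalent to about 22 m, which is larger than the minimum clinically important difference for the 2MWT". Allocation is equal: "Sixty patients (30 in the film + exercise hospital, 30 in the exercise-only hospital) will be recruited".

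The sentence names alpha but not its sidedness. It cites no baseline correlation, SD of change or other source of variance reduction.

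The Analysis section plans a repeated measures model for each outcome and reads the film effect from the interaction: "examining the hospital X time interaction will allow us to determine the additional effect of the film in addition to the exercise intervention". It states no direction for that test.

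**The concern.** An alpha of 0.05 with no qualifier is normally read as two-sided. On that reading a standardised difference of 0.65 needs visibly more than 30 patients per arm, so the stated inputs do not give the stated output.

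The power statement also concerns a plain difference between hospitals, whereas the film effect is to be taken from a difference in change over time. The two contrasts have different variances, so the power of one does not carry over to the other.

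At stake is how readers judge the precision of the trial on its primary quantitative outcome. On the two-sided reading, the chance of missing a true 0.65 SD difference is about 30%, not 20%.

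**Working it through.** **Inputs, all from the Sample size section**

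- Alpha 0.05, sidedness not stated; power 80%.
- Standardised difference d = 0.65, put at about 22 m, so the implied SD is 22 / 0.65 = 33.8 m.
- n = 30 per arm, 1:1, no inflation for attrition.

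**Step 1. Reproduce the stated figure.** For two independent means, the normal approximation is n per arm = 2(z_alpha + z_beta)² / d², with z_beta = 0.8416 for 80% power.

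- One-sided 0.05: 2(1.6449 + 0.8416)² / 0.4225 = 29.3, rounded up to 30. The exact calculation (noncentral t) gives 29.97.
- Two-sided 0.05: 2(1.9600 + 0.8416)² / 0.4225 = 37.2, rounded up to 38. The exact calculation gives 38.14, rounded up to 39.

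The one-sided result matches the stated figure almost exactly. The two-sided result is 8 to 9 patients per arm higher, which is more than the word *about* can cover.

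**Step 2. Power at 30 per arm.** The noncentrality is d / √(2/n) = 0.65 / √(2/30) = 0.65 / 0.2582 = 2.517, with 58 degrees of freedom.

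| Test at alpha 0.05 | Power, noncentral t | Power, normal approximation |
|---|---|---|
| One-sided | 80.0% | 80.9% |
| Two-sided | 69.7% | 71.1% |

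**Step 3. Difference detectable with 80% power, two-sided, 30 per arm.** Solving the noncentral t gives d = 0.736, which is 0.736 × 33.8 m = 24.9 m.

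**Step 4. Expected precision.** The 95% confidence interval half-width for an unadjusted difference is t(0.975, 58) × √(2/30) = 2.002 × 0.2582 = 0.517 SD, or about 17.5 m.

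**Step 5. The contrast that will be analysed.** For a difference in change from baseline, with equal SDs at both times and baseline-to-follow-up correlation rho, the standardised effect is d = 0.65 / √(2(1 − rho)). The article gives no rho, so the values below are assumptions. Power is two-sided at 30 per arm (noncentral t).

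| Assumed rho | d for change | Power |
|---|---|---|
| 0.3 | 0.549 | 55% |
| 0.5 | 0.650 | 70% |
| 0.6 | 0.727 | 79% |
| 0.8 | 1.028 | 97% |

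If the analysis is instead adjusted for baseline, d = 0.65 / √(1 − rho²). At an assumed rho of 0.5 this is 0.751, with power 81.6%.

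All figures treat patients as independent within a hospital. With one hospital per arm, that is itself an assumption.

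**The case against.** Four points can be made for the plan.

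1. *The number reproduces, so it is not an arithmetic slip.* This is fair as far as it goes: 29.97 is too close to 30 for coincidence to be the natural explanation, and a one-sided calculation reported without its label is the likely origin. But the article nowhere declares a one-sided test. A figure that fails under the conventional reading needs its label, and that is more than a detail left to an analysis plan.

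2. *The planned model may recover the power.* It may. A reader might infer from Step 2 that only a one-sided test can reach 80%, or that the trial as a whole is underpowered. The documents do not support either. With baseline adjustment at a correlation of about 0.5, or a change score at slightly above 0.6, two-sided power reaches about 80%. These correlations are assumed and the sentence invokes none, so they do not rescue it as written. They do confine the finding to the unadjusted comparison that it describes.

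3. *This is an early-phase trial, and 30 per site has its own justification.* This stands, and it is why the sample size need not change. It does not make the added power claim correct.

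4. *No harm follows.* A reader might infer that a null 2MWT result would be over-read as evidence against the film. The Analysis section stresses estimating change and effect sizes and sets no such rule, so that consequence is speculative. Two further charges should not be pressed. Attrition is openly discussed, and its estimation is made a feasibility aim. Power at the minimum clinically important difference cannot be quantified, because the article does not give that value.

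**Conclusion.** The power statement is wrong as written under the usual reading of alpha. For an unadjusted comparison of two groups of 30 with independent patients, two-sided power at 0.65 SD is about 70%, roughly 10 percentage points below the stated figure. The stated 80% belongs to a difference of about 0.74 SD (about 25 m), or to a one-sided test that the article does not declare. The metre values rest on the SD of 33.8 m implied by the article's own conversion.

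For the hospital by time contrast, the article supports no power figure. Over assumed correlations of 0.3 to 0.8, change-score power runs from 55% to 97%, so it could fall on either side of 80%.

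The point should be corrected, but it is of moderate weight: it alters neither the sample size nor the analysis.

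**What to change.** Keep 60 patients and reword the power sentence in one of two ways:

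- State that 30 per arm gives about 70% power at two-sided alpha 0.05 for a 0.65 SD (22 m) difference, or 80% power for about 0.74 SD (25 m); or
- Declare that the calculation is one-sided at 0.05, justify that choice, and make the planned test agree with it.

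In either case, say that the figures are for an unadjusted comparison that treats patients as independent, and give the expected 95% confidence interval half-width of about ±0.52 SD (17.5 m), which suits the estimation aim. If power is quoted for the between-hospital difference in change instead, state the assumed correlation or SD of change and show a range, as in Step 5.

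The cost is wording only. On the two-sided option the stated power becomes less favourable; recruitment, conduct and analysis are unaffected.

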### Analysis

Qualitative analysis will begin with an inductive descriptive process of sorting and defining the data [73]. Descriptive codes of analysis are attached to text segments, which will then be grouped into broad topic-oriented categories related to knowledge/attitudes, preferences and practices related to exercise, and barriers and facilitators regarding exercise participation and support. Text segments belonging to the same category will be compared within and across all participant interviews both within and between hospitals. Topic-oriented categories will be further refined and formulated into fewer analytical categories through an inductive, iterative process. The research team will develop the initial coding scheme. Each will independently open-code 25% [74] of interview transcripts, and then will meet to compare applied codes and to ensure consistency in interpretation. The remaining data will then be coded using NVivo 11 [75], a qualitative analysis software program. An audit trail will ensure analytic reliability through detailing: theoretical assumptions; codes, concepts and models; methodological and analytic procedures; and reflections on data collection. The audit trail will be reviewed by the research team to ensure analyses are supported by data [76]. In addition, two strategies to ensure internal and external validity will be used: triangulation [73]; and rich, thick description [77]. First, data triangulation involves using different data sets (e.g. family caregiver and patient interviews) to build coherent justification of interpretation. For example, if a patient discloses during the baseline interview that she is sedentary at home because of the injury-related fears of her family caregiver, but at 8 weeks demonstrates a significant improvement in community-based exercise, the patient’s and family caregiver’s interview transcripts will be analyzed to identify which specific components of *Fit for Dialysis* proved effective for the family caregiver at overcoming deficiencies in knowledge of the safety of exercise in settings beyond the outpatient clinic. Second, rich, thick description will be facilitated through the provision of verbatim quotes to allow readers to assess the strength of the relation between data and analysis.

Quantitative analysis of exercise prescription adherence (intradialytic and home/community exercise components) will be examined. To determine if patients are adherent to the intradialytic component, PTA-recorded minutes of intradialytic exercise performed each week will be compared to the prescription for that week (e.g. 50 min in week 3 were done, 60 min were prescribed, which is 83% adherent). Similarly, for the home/community component, adherence will be based on weekly number of minutes of exercise performed based on the GLTEQ results compared to the weekly exercise prescription. Multivariable logistic regression for each adherence variable will be performed at 8 weeks (mid-intervention), 16 weeks (end of intervention), and 12 weeks post-intervention including hospital as the main predictor. Covariates including age and sex will be included in the model based on clinical judgment guided by our prior work [19] and the literature.

To explore the impact of *Fit for Dialysis* on patient fitness and activity outcomes, while keeping in mind the phase of research, our focus is to estimate change in each of the 6 measures using a hospital X time linear repeated measures model for each outcome. The 2MWT is our primary outcome. Examining hospital-level effects will allow us to determine if the two hospitals were similar at baseline. Examining time effects within each hospital will provide information on the effects of the intervention in that hospital (film + exercise or exercise-only). Additionally, examining the hospital X time interaction will allow us to determine the additional effect of the film in addition to the exercise intervention. Since this is an early-phase intervention trial and it is unclear which of our quantitative outcomes will be most responsive in this population, we will also examine the responsiveness of each of the 6 outcome measures using standardized response mean to gauge whether the film + exercise is associated with a small, moderate, or large effect size [78] for each outcome. Covariates will be similar to Primary Objective 2. To examine the impact of adherence on the 2MWT, we will include a dichotomous variable reflecting global (intradialytic and home/community-based exercise considered together) adherence (yes/no). We will also explore including the two separate adherence components (intradialytic and home/community) in the repeated measures model, recognizing the risks of collinearity and model over-fitting (with 8 variables and 60 patients, including an interaction term between the two adherence variables).

As an exploratory analysis to get an initial sense of the temporal effects of both the film and the exercise program, we will calculate change scores for each of the 6 measures from baseline to 8 weeks, from 8 to 16 weeks, and from 16 weeks to 12 weeks after the end of the intervention (i.e. 28 weeks after baseline). An additional exploratory analysis will examine the six outcome measures (DASI, GLTEQ, TUG, 2MWT, Grip Strength, and pedometer) at 12 weeks after the end of the intervention. This analysis will consist of a linear repeated measures model similar to above, with two time points (8 and 16 weeks) and 12 weeks follow-up, and will examine whether any observed gains during the intervention period persist, continue to improve further, or become attenuated over time in both the film + exercise and exercise-only hospitals.

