### Individualized exercise program

The 16-week exercise program is based on a pilot exercise program [19] developed by research team members for the >65 years HD population. It focuses on muscular strength and flexibility, cardiovascular fitness, and functional capacity. The program consists of 20–30 min of cardiovascular exercise 2–3 times per week (40–90 min per week) and 10–15 min of strengthening 2–3 times per week (20–45 min per week) with an intensity of self-reported Rating of Perceived Exertion (RPE) of ‘light’ to ‘somewhat hard’ [36] and the ability to talk without difficulty while exercising. It is based on: (a) an individualized exercise prescription appropriate to each patient’s unique functional status and current activity level (identified by standard PT assessment [37] adjusting for individual participants’ comorbidities; (b) an exercise component, using Thera-Bands™ (rubber resistance tubing) and leg cycle ergometers, to be performed during dialysis sessions and supervised and logged by a PTA; c) an exercise component, using Thera-Bands, and to the greatest extent possible patients’ daily activities and available community resources, to be performed and logged by the patient at home/in the community; and (d) plain language information sheets that identify for patients and family caregivers clear parameters for patient exercise safety.

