*The Timed-Up-and-Go (TUG)*: The TUG is a test of basic mobility and reflects the ability to transfer from sitting to standing and to walk a short distance (3 m) and return to a seated position [54]. After a practice trial, the final two trials will be recorded and the best measure will be used for analysis [54]. Reliability and validity [55, 56] are well established. The TUG will be administered at baseline, 8 and 16 weeks, and 12 week after the end of the intervention.
*Godin Leisure-Time Exercise Questionnaire (GLTEQ)*: The GLTEQ is a simple 3-item measure assessing the frequency of mild, moderate, and strenuous bouts of exercise performed for at least 15 min in duration in a typical week. It will be used to capture a range of activities undertaken by patients (e.g. housework, recreational activities), as well as to compensate for the inability of the pedometer to capture exercise and activity undertaken in reclined positions during HD treatment, and possible non-adherence with wearing the pedometer. Co-I SA has successfully used this measure in exercise trials with adult cancer patients [57, 58]. It has also been validated in studies with older adults with other chronic illnesses [59–61]. On a weekly basis throughout the 16-week intervention, and at 12 weeks after the end of the intervention, the PTAs will contact patients by phone to record how much exercise was done that week using the GLTEQ [62].
*Pedometer*: Pedometers are a widely used method for inferring activity levels based on the number of steps taken throughout the day [63, 64] and considered the gold standard in physical activity measurement [65]. Patients will be asked to wear a pedometer for 1 week at baseline, and at the 8- and 16-week assessments, and 12 weeks after the end of the intervention (to facilitate comparison with the GLTEQ measured at those time points). The PTAs will download the data from the pedometer at each assessment point. Compliance with wearing a pedometer, and its validity as a measure of exercise have both been demonstrated in older adults with various chronic illnesses [64, 66].

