*Exercise Logs*: During the 16-week intervention, an intradialytic exercise log will be kept by the PTAs documenting exercises performed by the patients, as well as perceived exertion and heart rate. Patients will also be asked to keep a log of the exercises performed at home and in the community. The PTAs will review the exercise logs with the patients prior to each intradialytic exercise session to discuss any concerns.
*Adherence*: Adherence is important to assess as it is a necessary step to achieve gains in physical fitness (which would, in turn, lead to broader health benefits). However, there is no gold standard for assessing adherence to exercise, particularly in an elderly dialysis population. We have based our exercise prescription and definition of adherence on clinical judgement and prior experience providing exercise to frail older HD patients [19]. Adherence is thus defined as meeting at least 70% of the exercise prescription (recognizing that the number of minutes of prescribed exercise per week may change during the protocol as patients improve their fitness level with exercise), on average, over the 16-week intervention [67]. Given the separate components of exercise (intradialytic and home/community-based) that are being targeted by our intervention, we will include both a global adherence measure and separate adherence measures for the two exercise components (intradialytic and home/community). This same definition of adherence will be used for the intradialytic exercise and home/community exercise components. In addition, a global dichotomous measure of adherence will be used to facilitate inclusion in a multivariable model in which patients will be considered adherent overall if they are adherent (at least 70% of the exercise prescription) to both intradialytic and home/community exercise components, and non-adherent otherwise.

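### Home/community adherence is scored in minutes from the GLTEQ, which as described counts bouts of 15 min or more across all settings, so patients can be misclassified either way around the 70% cut

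*Protocol article*

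**What the plan says.** - **Analysis section.** The intradialytic component compares minutes recorded by the physiotherapy assistant (PTA) with that week's prescription. The rule for the other component reads: "adherence will be based on weekly number of minutes of exercise performed based on the GLTEQ results compared to the weekly exercise prescription". Logistic regressions for each adherence variable are planned at 8 weeks, 16 weeks and 12 weeks post-intervention, with hospital as the main predictor.
- **Data collection, GLTEQ entry.** The instrument has three items, "assessing the frequency of mild, moderate, and strenuous bouts of exercise performed for at least 15 min in duration in a typical week". It is meant to cover activities such as housework and recreation, and to "compensate for the inability of the pedometer to capture exercise and activity undertaken in reclined positions during HD treatment". It is given weekly: "the PTAs will contact patients by phone to record how much exercise was done that week using the GLTEQ".
- **Data collection, Adherence entry.** A patient is adherent at 70% or more of the prescription, averaged over the 16-week intervention. Intradialytic and home/community adherence are scored separately. The global dichotomous measure requires both.
- **Individualized exercise program.** Cardiovascular bouts are 20–30 min, and the programme also includes "10–15 min of strengthening 2–3 times per week". The home part may draw on daily activities and is logged by the patient.
- **Data collection, Exercise Logs entry.** "Patients will also be asked to keep a log of the exercises performed at home and in the community". The PTAs go through the logs with patients before each intradialytic session. Table 1 and its footnotes show the logs ending with the intervention, while the GLTEQ is repeated 12 weeks later.

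**The concern.** The endpoint is minutes of home/community exercise. The named source, as described, is a count of bouts, with a minimum length and no restriction to home or community. Three mismatches follow.

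- **Units.** No rule turns a bout count into minutes.
- **Floor.** A strengthening bout of 10–14 min done on its own meets the prescription but is not a countable bout.
- **Setting.** Exercise during dialysis is within what the GLTEQ is meant to capture, and no rule takes it out of the home score. The same applies to activity that was not prescribed.

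Quantifying adherence is part of Primary Objective 2. The score feeds the home/community logistic model, the global yes/no measure and the adherence terms in the 2MWT model. If the film raised intradialytic exercise only, uncorrected GLTEQ bouts could make that look like a home/community effect, which is the distinction the separate measures exist to draw.

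**Working it through.** **The plan's own figures.** The worked example of weekly adherence is 50/60 = 83%, which reproduces. So do the weekly ranges: cardiovascular 2 × 20 = 40 to 3 × 30 = 90 min, and strengthening 2 × 10 = 20 to 3 × 15 = 45 min.

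**Assumption.** The article gives these ranges for the programme as a whole and does not state the home share. They are applied to the home component below for illustration only.

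**Under-count.** A patient does everything prescribed: cardiovascular bouts of c min and separate strengthening bouts of s min, each f times a week. Prescribed minutes are f(c + s). When s is below 15, only the cardiovascular bouts count, and f cancels:

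- true minutes known for each counted bout: c/(c + s)
- each counted bout credited at the 15-min minimum: 15/(c + s)

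When s = 15 both bouts count, giving 100% and 30/(c + s).

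| c + s (min) | True minutes for counted bouts | 15-min credit |
|---|---|---|
| 20 + 10 | 20/30 = 67% | 15/30 = 50% |
| 20 + 14 | 20/34 = 59% | 15/34 = 44% |
| 20 + 15 | 35/35 = 100% | 30/35 = 86% |
| 30 + 10 | 30/40 = 75% | 15/40 = 37.5% |
| 30 + 14 | 30/44 = 68% | 15/44 = 34% |
| 30 + 15 | 45/45 = 100% | 30/45 = 67% |

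With true minutes, a fully compliant patient falls below 70% when c/(c + s) < 0.70, that is s > 3c/7. For c = 20 the limit is 8.6 min, so every separate bout of 10–14 min fails. For c = 30 it is 12.9 min, so only bouts of 13–14 min fail. If strengthening and cardiovascular work are done as one session, nothing is dropped. A 15-min credit would then give 15/45 = 33% to 15/30 = 50%.

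**Over-count.** A patient does no home exercise, but three intradialytic bouts are reported on the GLTEQ and not excluded. The score is 3m/P, where m is the minutes credited per bout and P is an assumed weekly home prescription.

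| m (min) | P = 60 min | P = 90 min |
|---|---|---|
| 15 | 45/60 = 75% | 45/90 = 50% |
| 20 | 60/60 = 100% | 60/90 = 67% |
| 30 | 90/60 = 150% | 90/90 = 100% |

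So a patient with no home exercise can land on either side of 70%, depending on m and P.

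**The case against.** The best defence is that an article condenses the full protocol and the call form is not shown. The PTAs record how much exercise was done, so they may ask for duration. They also supervise and log the intradialytic sessions, so they could leave those out when scoring a component labelled home/community. The article concedes that exercise adherence has no gold standard, and weekly recall taken by staff is a defensible alternative to a patient diary. The main hospital × time comparison of the 2MWT does not use this variable.

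Much of this stands, and it rules out several stronger readings that a reader might infer:

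- *Intradialytic sessions are counted twice.* No passage says so. What the text supports is that the GLTEQ is meant to capture them and no exclusion is stated.
- *The GLTEQ can yield no minutes.* Duration may be asked on the call. It is simply not part of the instrument as described.
- *Counting housework is an error.* The home component may use daily activities, so only unprescribed activity is a problem.
- *Prescribed strengthening is lost.* Only separate bouts under 15 min are. A 15-min bout counts, and so does strengthening joined to cardiovascular work.
- *A compliant patient on 30 + 10 min is called non-adherent.* That requires the 15-min credit, which appears nowhere in the article. With true minutes the score is 75%.

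The defence does not remove the core. The article names both the source and what it records, so this is a stated mismatch and not detail left to a fuller document. Asking for duration would cure the units, but not the 15-min floor or the missing separation by setting.

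**Conclusion.** The rule is wrong as written: the instrument named for home/community minutes does not, as described, measure home/community minutes. Misclassification can run in both directions across the 70% cut, and it carries into the global yes/no measure and the models that use either variable.

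The under-count does not depend on any bout-to-minute convention: 67% for full compliance with separate 20 + 10 min bouts. It does assume that the programme's ranges apply to the home component and that the two kinds of exercise are done separately. The over-count is conditional. It needs intradialytic bouts to remain in the score, and at 15 min per bout it runs from 75% against 60 min to 50% against 90 min. A further caution is that three intradialytic cardiovascular bouts may already use up the programme's 2–3 per week, so the added home prescription is itself an assumption. How many patients would be misclassified cannot be estimated from the article. The primary 2MWT comparison between hospitals is unaffected, except where adherence terms are added to that model.

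**What to change.** - For the 8- and 16-week analyses, define home/community adherence as Home/Community Log minutes divided by that week's prescribed home/community minutes. This parallels the intradialytic rule.
- Require the home log to record minutes per session. The article says only that exercises are logged.
- Keep the GLTEQ as a total-activity outcome and as a sensitivity check on the log, with intradialytic bouts excluded and the bout-to-minute conversion written down.
- Either drop the 12-week post-intervention home/community adherence model or relabel it as an analysis of GLTEQ activity. The logs end at week 16, and adherence is defined over the 16-week intervention.

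The cost is a minutes field on the log, entry of those data and a revised analysis rule. No new visit or instrument is needed. The downside is reliance on patient-completed logs, eased by the PTA review already planned before each intradialytic session.
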